# Warm homes for older people: aims and methods of a randomised community-based trial for people with COPD

**DOI:** 10.1186/1471-2458-13-176

**Published:** 2013-02-26

**Keywords:** New Zealand, COPD, Housing, Health, Fuel poverty, Randomised community trial

## Abstract

**Background:**

Chronic Obstructive Pulmonary Disease (COPD) is of increasing importance with about one in four people estimated to be diagnosed with COPD during their lifetime. None of the existing medications for COPD has been shown to have much effect on the long-term decline in lung function and there have been few recent pharmacotherapeutic advances. Identifying preventive interventions that can reduce the frequency and severity of exacerbations could have important public health benefits. The Warm Homes for Elder New Zealanders study is a community-based trial, designed to test whether a NZ$500 electricity voucher paid into the electricity account of older people with COPD, with the expressed aim of enabling them to keep their homes warm, results in reduced exacerbations and hospitalisation rates. It will also examine whether these subsidies are cost-beneficial.

**Methods:**

Participants had a clinician diagnosis of COPD and had either been hospitalised or taken steroids or antibiotics for COPD in the previous three years; their median age was 71 years. Participants were recruited from three communities between 2009 to early 2011. Where possible, participants’ houses were retrofitted with insulation. After baseline data were received, participants were randomised to either ‘early’ or ‘late’ intervention groups. The intervention was a voucher of $500 directly credited to the participants’ electricity company account. Early group participants received the voucher the first winter they were enrolled in the study, late participants during the second winter. Objective measures included spirometry and indoor temperatures and subjective measures included questions about participant health and wellbeing, heating, medication and visits to health professionals. Objective health care usage data included hospitalisation and primary care visits. Assessments of electricity use were obtained through electricity companies using unique customer numbers.

**Discussion:**

This community trial has successfully enrolled 522 older people with COPD. Baseline data showed that, despite having a chronic respiratory illness, participants are frequently cold in their houses and economise on heating.

**Trial Registration:**

The clinical trial registration is http://NCT01627418

## Background

Reducing the impacts of chronic diseases is a growing problem. By 2030, Chronic Obstructive Pulmonary Disease (COPD) is projected to become the third most common cause of death globally with about one in four people estimated to be diagnosed with COPD during their lifetime [1,2]. The main characteristics include a progressive, irreversible decline in lung function, accompanied by breathlessness, a chronic cough and increased sputum production. Exacerbations, or acute worsening of the symptoms, which lead to a decrease in health-related quality of life, are part of the natural history of the disease [3]. While smoking is a major cause, there is a strong social gradient in COPD mortality, independent of smoking [4,5].

None of the existing medications for COPD has been shown to have much effect on the long-term decline in lung function and there have been few pharmacotherapeutic advances [6]. Identifying preventive interventions that can reduce the frequency and severity of exacerbations could have important public health benefits.

### The cost of COPD to society

COPD is a leading reason for admission to hospital, acute visits to outpatient and emergency departments and family doctors. It is estimated that about half the average COPD costs are due to hospitalisation and the annual hospitalisation costs for a severe COPD patient are about six times greater than those for a patient with mild or moderate COPD [7]. National direct and indirect annual costs vary from approximately $US37.2 billion in an American study [8] to between $A0.8 and $A1.0 billion per year in an Australian study [9].

In New Zealand, COPD is among the top four major causes of avoidable hospitalisation, with COPD-related hospitalisations rising rapidly over the last two decades. Depending on assumptions about costings and average length of stay, direct treatment cost estimates range from $NZ16.4 million in 1998/9 [10], to $NZ102-192 million in 2003 [1].

### COPD and housing

A number of studies have linked socio-economic status (SES) with respiratory illness [11] and specifically COPD [4,12-15], but few studies have looked at possible links between housing conditions and exacerbations of COPD. A review of socio-economic determinants of COPD [16] looked at home conditions and behaviours, but only one paper specifically included a housing quality measure (summarised as years without central heating) which was significantly inversely related to lung function [17].

Studies relating housing and health often use housing as a marker for SES, rather than exploring the role of the housing itself [18]. In addition, studies that have examined the role of housing in COPD often use only a single housing variable. Three studies, using different housing measures - a composite variable (number of rooms and sector of landlord) [19]; two binary indicators of housing quality (presence of central heating and one or more rooms per person) [4]; and the number of people living at home [12] -- did not find any observed relationship with COPD. One set of papers [20,21] followed COPD patients through an energy efficiency upgrade; this is reviewed further below.

A review looking at improving life for COPD patients only mentioned the home in terms of therapies taken there [22]. Another review found that only one of 171 papers referred to the home environment (temperature) [23]. Nonetheless, Burge suggests the way forward is a combination of interventions including warmer housing [24].

### Temperature and respiratory illness

There is a clear association between a cold environment and morbidity both generally [25] and for people with COPD [26] during winter in particular [27,28]. COPD patients who experience frequent exacerbations are more likely than those with less frequent exacerbations to acquire a cold, but both groups have approximately the same rates of COPD exacerbations once the cold has been acquired [29,30]. Therefore, reducing the risk factors associated with common winter respiratory diseases might have a disproportionately advantageous effect on individuals with COPD.

In New Zealand, the excess winter hospitalisation rate for COPD is 70% (rate ratio 1.70, 95% CI 1.67, 1.73 for 2000–2004) (Zhang, Viggers et al., submitted). New Zealand also has a greater seasonality of mortality, driven by effects on those over 65, than the more extreme climates of the United Kingdom, the United States, Australia, Japan or Sweden [27,31]. People over the age of 80 have an approximately 74% increased chance of dying of respiratory disease in winter rather than other seasons [31,32]. A study linking census and mortality data showed an increased risk of dying in winter among low-income people, those living in rented accommodation and those living in cities [33]. Such excess winter mortality also applies to cardiovascular diseases, but not to non-housing related diseases, such as cancer. These findings suggest modifying people’s heating behaviour in winter might result in reduced rates of illness and possibly mortality.

### Temperature of New Zealand homes

Compared to other countries with similar climates, houses in New Zealand are colder, with an *average* winter evening living room temperature of 17.9°C and a mean range of 10°C- 23.8°C [34]. Often only one room, usually the living room, is heated during winter [35]. Average winter overnight bedroom temperatures fall below 14°C [36], indicating that many bedrooms are colder than this for all or part of winter.

The World Health Organization included the elderly in groups vulnerable to low indoor temperatures in the home, and stated that below 16°C there was a serious risk to health, and between 16°C and 19°C there were small risks to health after substantial periods of time [37]. In England and Wales if people are home all day acceptable temperatures are defined as 21°C in the main living area and 18°C in other occupied rooms [38], but the New Zealand Building Code’s only relevant specification is that the interior temperature of old people’s homes and early childhood centres should be able to be maintained at a minimum of 16°C [39].

There are suggestions that higher morbidity, as well as mortality, may be compounded by energy-inefficient or poorly heated housing, particularly for older people [40-43]. Research we have previously conducted found that insulating houses led to a significantly warmer, drier indoor environment and resulted in improved health and a trend for fewer hospital admissions for respiratory conditions [44,45]. The addition of more effective, sustainable heating, as well as retrofitted insulation, in houses where there were children with asthma problems, reduced asthma symptoms, visits to the doctor and school absences [46].

### Fuel poverty and increasing electricity prices

Poorly heated housing is influenced by three factors: the thermal quality of the house; the income of the occupants; and the price of fuel [47]. Britain has developed comprehensive policies to address fuel poverty, defined as households where more than 10% of income must be spent to achieve adequate temperatures, although that definition is currently subject to debate [48,49]. Policies include a universal non-means-tested, non-taxable Winter Fuel Allowance for households containing people aged over 60, improvement in the quality of social housing, and energy efficiency measures [38,50].

A model of the effect of the Winter Fuel Allowance [51] drew on the concept of mental accounting, a term coined by Thaler to describe models and rules that individuals use to organise their finances [52,53]. Munro and colleagues hypothesised that while there was no requirement that the Fuel Allowance *would* be spent on fuel bills, there was some evidence that money labelled as a ‘fuel allowance’ and nominally allocated to this particular area of expenditure was more likely to be spent there, so may be an effective way to increase warmth. Moreover, English households that receive heating and insulation interventions have shown greater increases in warmth than those that received insulation interventions alone [54].

Fuel poverty has been established as an increasing problem in New Zealand, with potentially 25% of households meeting this definition in 2008, up from 12% in 2001. With the rising price of energy, its incidence and severity are increasing [55]. In the last decade, nominal average retail electricity prices increased over 80% [56], and real prices by 40%.

The cost of electricity has been rising faster than inflation-adjusted superannuation leading to particular difficulties for older people, who may be on fixed incomes and lack the physical strength to use fuels such as wood or wood pellet bags [57]. The use of wood heaters is also problematic for COPD patients as indoor air pollution can trigger exacerbations [58].

The Ministry of Social Development’s Economic Living Standard Index, which provides a scale applicable to the general population, has two items pertinent to fuel poverty: “put up with cold” and “stayed in bed for warmth” [59]. This underlines that among poorer New Zealanders domestic warmth is not always affordable.

### Housing interventions for people with COPD

Possible links have long been made between cold housing and COPD exacerbations for example, in indoor environments which are cold with high relative humidity, mattresses can become very damp and cold [60]. For people with COPD, maintaining the WHO warmth guideline of 21°C in living areas for at least nine hours per day was associated with better health status [20]. Donaldson and colleagues also showed a small increase in lung function for patients with COPD, when there was a similar rise in indoor bedroom temperature [26].

Following these associations, Osman and colleagues conducted a small community trial to investigate the effect of increasing indoor temperatures on COPD through home energy improvements. Despite significant implementation barriers, when the improvements were made there was an improvement in respiratory health [21] suggesting a larger trial would be warranted.

## Methods/Design

The Warm Homes for Elder New Zealanders (WHEZ) study is a community-based trial designed to test whether an electricity voucher paid into the electricity account of older people with COPD, with the expressed aim of enabling them to keep their homes warm, results in reduced exacerbations.

Ethical consent was obtained from the New Zealand Multi-Region Ethics Committee MEC/07/05/062 and the Clinical Trial Registration is NCT01627418. Written informed consent was gained from the participants.

### Research questions

The primary research question is whether the provision of an electricity subsidy reduces exacerbations of COPD requiring hospitalisation, or treatment with corticosteroids and/or antibiotics. Secondary questions include whether the dwelling temperature is affected by the electricity intervention and whether the estimated benefits of the intervention exceed the costs.

### Intervention

The intervention is a subsidy of NZ $500 (approximately US $400, £250, €300) towards the household electricity bill, which was calculated as being sufficient for a 2.4 kW electric heater to run continuously for an additional 10 hours a day for 12 weeks, thus raising the temperature of one room substantially, as well as the overall average indoor temperature. The money was paid directly into the household’s electricity account (in the first winter of enrolment for the early group, and the second for the late group). $500 was considered a potentially feasible sum for the government to implement as a national policy and is comparable to the British Winter Fuel Subsidy.

The amount was tied to the electricity bill, as subsidising other common forms of heating, such as wood or liquefied petroleum gas, would potentially have a deleterious effect on indoor air quality, which might adversely affect the participants’ lung function. Initial feedback on this method of subsidy has been positive; there have been very few calls to our phone helpline from people expecting the payment to be made another way.

Due to the complexity of New Zealand’s deregulated domestic electricity industry, which includes competing electricity retailers, organising and implementing the intervention was not a trivial task. However, close liaison with the electricity companies proved worthwhile and most were very co-operative. For example, company representatives, who understood the study, referred back to the study team a request from a participant to withdraw some of the credited money from their account.

### Sample size

The primary outcome of concern was the rate of moderate or severe COPD exacerbations amongst the participants. The TORCH study of combined long-acting beta agonists and corticosteroids found yearly moderate or severe exacerbation rates dropped from 1.13 in the placebo group to 0.85 in the combination therapy group, giving a rate ratio of 0.75 [61]. The study was sized to duplicate a reduction of this size – using a negative binomial model for exacerbation rates as recent analyses have used these, rather than Poisson models, as the negative binomial models better account for individual patient variability [61,62]. A “k” parameter (the shape parameter of the associated gamma distribution) of 0.46 was used as a reanalysis of the TRISTAN data found this the most appropriate (95%CI 0.34-0.60) [62]. These parameters, with a confidence level of 95% and a power of 80% yield an estimated required group size per arm of 239, which allowing for a 15% drop out rate (greater than the 10% found in the *Housing, Insulation and Health study* for the over 65s due to the greater illness of this study population) suggested an initial sample size of 550 participants. If the “k” parameter was 0.4 then the required group size per arm would have been 230, if 0.6 then it would have been 262. If the baseline exacerbation rate was 1.0 rather than 1.13 then the required group size per arm would be 260. Therefore 550 participants was the target sample size.

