### Wave design and randomisation

As winter was the crucial period for the study, and recruitment is often slow at the start of the process the study was deliberately designed to recruit over two years in ‘waves’. Participants were recruited from three communities from 2009 to early 2011. Those recruited (i.e. consent and baseline data received) by June (early winter in the southern hemisphere) 2010 were assigned to Wave 1, those recruited later were assigned to Wave 2. Each wave was randomised into early and late intervention groups – the early group receiving the intervention the first winter in which the wave was enrolled in the study, and the late group the following winter. Thus *Wave 1- Early* participants received the fuel subsidy during 2010; *Wave 1- Late* and *Wave 2- Early* participants received the subsidy during 2011; *Wave 2- Late* participants received the subsidy during the winter of 2012. The randomisation was carried out by a statistician external to the study team.

The configuration of an autumn baseline with a spring follow-up was chosen in recognition of the significant illness of the sickest participants; with a full winter baseline there could have been more of a bias towards only the least unwell people completing the study. We allowed for a greater drop-out rate than we usually experience due to the illness among the study population.

As the intervention was carried out at a dwelling level, in order to avoid clustering, we selected only one primary participant per household, the person best able to complete the study questionnaire. The baseline interviews were carried out before randomisation so that knowledge of their group allocation could not affect the participants’ measures. In order to utilise the voucher for additional heating, the participants were then informed of their group allocation. Although the interviewers also knew the participant’s group allocation, they were trained to avoid mentioning group allocation status during interactions with the participants to minimise any recall bias. The analyses will be carried out with the researchers blinded to the meaning of the intervention group code. We also included several indicators designed to measure each participant’s propensity to report positive change and will control for the placebo effect by conducting sensitivity analyses using these propensity to positivity scores.

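### The sample size uses a full-year event rate and a full-year effect for a one-winter credit, so the parallel comparison does not reach the stated 80% power on the plan's own inputs

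*Protocol article*

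**What the plan says.** The Sample size section takes both planning rates from a trial of daily drug treatment, which "found yearly moderate or severe exacerbation rates dropped from 1.13 in the placebo group to 0.85 in the combination therapy group". The article puts the ratio of these two rates at 0.75. It then says: "The study was sized to duplicate a reduction of this size". The negative binomial k is 0.46. The calculation is made "with a confidence level of 95% and a power of 80" per cent and yields 239 per arm. No follow-up time enters it.

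The Intervention section describes one NZ$500 credit per household, calculated as enough for a heater "to run continuously for an additional 10 hours a day for 12 weeks". The early group receives it in its first winter and the late group in its second. The Wave design and randomisation section calls winter the crucial period and adds: "The configuration of an autumn baseline with a spring follow-up was chosen". In the Background, under Temperature and respiratory illness, "the excess winter hospitalisation rate for COPD is 70" per cent (rate ratio 1.70). Table 2 defines the primary outcome as a number of moderate and severe exacerbations, without a period over which they are counted.

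**The concern.** A count trial gets its information from the number of events in the window compared and from the size of the effect in that window. The plan takes both from a setting where treatment and counting ran all year. Here the treatment is aimed at one winter, and the arms differ in voucher receipt only until the late group's winter. A winter-length count gives each participant fewer than 1.13 events if the planning rate is right. A year-long count keeps the events but dilutes an effect confined to winter. Either way, the 80% power belongs to a different exposure. A reader of a null result who relies on 80% power for a 25% reduction would take it as stronger evidence of no benefit than the design can give.

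**Working it through.** **Inputs.** From Sample size: control rate 1.13 per year, RR 0.75, k = 0.46, 239 per arm. From the Background: winter ratio 1.70, reported for hospitalisations only. Assumed here: a two-sided test (the article does not state sidedness), equal arms, and windows of 12 weeks, 4 months and 6 months.

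**Formulas** (Wald test of the log rate ratio; μ = expected events per control in the window):

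- V = 1/μ + 1/(μ·RR) + 2k
- n per arm = (1.960 + 0.842)² × V / (ln RR)², where (1.960 + 0.842)² = 7.849
- power = Φ(|ln RR| / √(V/n) − 1.960)

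The article calls k a gamma shape parameter. Its required n rises with k, so k acts as the dispersion (variance = mean + k × mean²) and is used that way here.

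**1. The plan's own figure.** With μ = 1.13 and RR = 0.75, V = 0.885 + 1.180 + 0.920 = 2.985 and (ln 0.75)² = 0.0828. Then n = 7.849 × 2.985 / 0.0828 = 283 (289 with RR = 0.85/1.13), so 239 does not reproduce. Taking the null variance from the reference rate gives 263–269, and one-sided variants give 208–229.

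The one-year exposure can still be confirmed. The article gives 230 for k = 0.4 and 262 for k = 0.6, so the ratios to 239 are 0.962 and 1.096. V for one year gives 2.865/2.985 = 0.960 and 3.265/2.985 = 1.094. For half a year (μ = 0.565) it would give 4.930/5.050 = 0.976 and 5.330/5.050 = 1.055. All four stated sizes (239, 230, 262, 260) fit a one-year exposure, with 6.61–6.64 in place of 7.849.

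Power at 239 for a full year and a full-year effect: 0.2877 / √(2.985/239) − 1.960 = 0.614, which gives **73%**. A one-sided test would give 82%.

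**2. Counting a winter window, RR 0.75 inside it.** For a winter of w months with the 1.70 excess applied to all events, share of annual events = 1.70w / (1.70w + 12 − w). Without the excess, share = w/12. μ = 1.13 × share.

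| Window | Share | μ | V | Power at 239 | n per arm for 80% |
|---|---|---|---|---|---|
| 12 weeks, excess 1.70 | 0.338 | 0.382 | 7.03 | 0.389 | 667 |
| 4 months, excess 1.70 | 0.459 | 0.519 | 5.41 | 0.481 | 513 |
| 6 months, excess 1.70 | 0.630 | 0.711 | 4.20 | 0.583 | 398 |
| 12 weeks, no excess | 0.231 | 0.261 | 9.87 | 0.293 | 936 |
| 4 months, no excess | 0.333 | 0.377 | 7.12 | 0.385 | 675 |
| 6 months, no excess | 0.500 | 0.565 | 5.05 | 0.508 | 479 |

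**3. Counting a full year, effect in the winter window only.** Annual RR = 1 − 0.25 × share, with the 1.70 excess: 0.916, 0.885 and 0.843 for 12 weeks, 4 months and 6 months. With μ = 1.13 and 239 per arm, power is 0.127, 0.202 and 0.347.

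**4. Detectable rate ratio.** Solving the n formula for RR at n = 239 and 80% power gives 0.73 for a full year, and 0.60, 0.65 and 0.68 for the three winter windows with the excess.

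**The case against.** A reader might infer that the randomised contrast is one winter and that the real power is therefore 39–58%. The article does not support so firm a statement, for five reasons.

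- **No window is fixed.** The autumn and spring visits describe when participants were interviewed. The late group has no voucher until its second winter, so close to 12 months of parallel comparison is possible, and hospital and primary care records could supply the events.
- **Twelve weeks is how the sum was costed.** It is not a limit on when the credit could be spent.
- **The winter event rate is assumed.** The 1.70 ratio is for hospitalisations, while the primary outcome also counts steroid and antibiotic courses. In Table 1, 22% reported four or more bouts of severe chest trouble over winter, which alone implies at least 4 × 0.22 = 0.88 bouts per person. Self-reported bouts are not treated exacerbations, but the signal lies above every μ in the table. At μ = 0.88 one-winter power is about 65%, and at 1.5 about 81%.
- **Both winters could be used.** Each participant has one winter with the voucher and one without. If individual rates are stable, there is no carry-over and second-winter data are complete, the log ratio of winter counts within an arm has variance v = (1/μ + 1/(0.75μ))/239. The standard error of ln RR is then √(2v)/2. Power is about 72%, 84% and 93% at μ = 0.382, 0.519 and 0.711.
- **Part of the gap is not seasonal.** The drop from 80% to 73% is there with a full year counted.

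All five stand as limits on the size of the shortfall, but they do not rescue the stated 80%. The section sizes a parallel comparison per arm, and Data analysis lists study arm as a covariate with no period or within-person term. Extending the count to 12 months dilutes the effect unless the benefit outlasts the heating. Nor is this a detail that a condensed article may leave out: the article presents a sample size calculation, and its time basis does not match the intervention and follow-up described beside it.

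**Conclusion.** The point holds as a conditional statement. For a two-sided parallel comparison with 239 per arm and the article's own rate, dispersion and 25% reduction, the stated 80% is not reached on any of the three readings checked: a full year with a lasting effect, a winter window, or a full year with a winter-only effect. The most favourable, at 73%, needs a winter heating credit to cut exacerbations by a quarter all year. The two winter-based readings range from 13% to 58%, depending on the window, the winter excess and how long the effect lasts.

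No single value in that range can be called the trial's power. A control winter rate near 1.5 or a two-winter analysis could bring power to 80% or above, but the article plans for neither.

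**What to change.** In Sample size and Table 2, state the counting window and exposure time for the primary comparison, with the same calendar dates in both arms within each wave. One option is the first winter, from voucher credit to spring follow-up; the sponsor may justify another. Restate power and the detectable rate ratio for that window as a range over the assumed winter event rate, with the test's sidedness and the formula given so that the figure can be reproduced. Remove the unqualified claim of 80% power for an annual rate ratio of 0.75. If a two-winter analysis is intended, say so in Data analysis and compute power for it, with its assumptions on carry-over and stable individual rates.

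The cost is wording and a recalculation. Enrolment is complete at 522, so the size does not change and no new data or patients are needed. The drawback is that the stated power becomes less favourable.

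### Sample size: k = 0.46 is defined as the gamma shape, but the stated sizes rise with k, as only the dispersion (the reciprocal of the shape) allows

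*Protocol article*

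**What the plan says.** All the relevant text is in the Sample size section of the protocol article.

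- Effect: yearly rates that "dropped from 1.13 in the placebo group to 0.85 in the combination therapy group, giving a rate ratio of 0.75".
- Model: "using a negative binomial model for exacerbation rates".
- Variability: "A “k” parameter (the shape parameter of the associated gamma distribution) of 0.46 was used", because "a reanalysis of the TRISTAN data found this the most appropriate (95%CI 0.34-0.60").
- Result: these inputs, "with a confidence level of 95% and a power of 80% yield an estimated required group size per arm of 239".
- Sensitivity to k: "If the “k” parameter was 0.4 then the required group size per arm would have been 230, if 0.6 then it would have been 262".
- Sensitivity to the rate: "If the baseline exacerbation rate was 1.0 rather than 1.13 then the required group size per arm would be 260".

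After an allowance for dropout, the target is 550. The section gives no variance formula, sidedness or follow-up time per person.

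**The concern.** In a gamma-Poisson (negative binomial) model with mean mu, two conventions are in use. If k is the gamma shape, the variance is mu + mu²/k. If k is the dispersion, the variance is mu + k·mu². Each is the reciprocal of the other, so reading 0.46 as a shape implies a dispersion of 1/0.46 = 2.17, which is 4.7 times 0.46.

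The text names the first convention and its sizes behave like the second. This matters because k is the only variability figure behind the 80% power and the 550 target, and because a confidence interval and a sensitivity analysis are attached to it. Under the printed definition the demanding end of that interval is the low one (0.34), whereas the sensitivity figures make k = 0.6 the demanding case. Anyone who re-derives the power from the text as written will not get 80%.

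**Working it through.** **Inputs from the Sample size section:** rates 1.13 and 0.85 per year; k = 0.46, interval 0.34 to 0.60; 80% power; 95% confidence.

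**Assumed, because not stated:** two-sided 5%, equal arms, t = 1 year per person (the rates are yearly), Wald test on the log rate ratio.

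**Formula.** With dispersion d,

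n per arm = (1.960 + 0.8416)² × [1/(1.13t) + 1/(0.85t) + 2d] / [ln(0.85/1.13)]²

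Here (1.960 + 0.8416)² = 7.849, ln(0.85/1.13) = −0.2847 and its square is 0.08107, so the multiplier is 96.81. At t = 1 the Poisson part is 0.8850 + 1.1765 = 2.0614.

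**Step 1: direction.** The shape reading sets d = 1/k and the dispersion reading sets d = k.

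| k | stated | d = k | d = 1/k |
|---|---|---|---|
| 0.40 | 230 | 277.0 | 683.6 |
| 0.46 | 239 | 288.6 | 620.5 |
| 0.60 | 262 | 315.7 | 522.3 |

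For k = 0.46:
- as a dispersion, 96.81 × (2.0614 + 0.92) = 288.6;
- as a shape, 96.81 × (2.0614 + 4.3478) = 620.5.

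The stated sizes rise with k. The dispersion column rises and the shape column falls. The sign of the trend does not depend on t, sidedness or power, because k enters only through 2d.

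**Step 2: can the shape reading give 239 at all?** A longer t shrinks only the Poisson part. At t = 2 the need is 96.81 × (1.0307 + 4.3478) = 520.7. With unlimited follow-up it is 96.81 × 4.3478 = 420.9. A one-sided 5% test at one year needs about 489. None is near 239.

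**Step 3: does the dispersion reading give 239?** In direction yes, in level no. The ratios of stated to computed size are 230/277.0 = 0.830, 239/288.6 = 0.828 and 262/315.7 = 0.830. With a baseline rate of 1.0 and the same rate ratio, the computed size is 314.6 and 260/314.6 = 0.827. A one-sided 5% test gives about 227 at k = 0.46.

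A longer follow-up would close the gap at k = 0.46. Solving 96.81 × (2.0614/t + 0.92) = 239 gives t = 1.33 years. At that t, k = 0.4 gives 227, k = 0.6 gives 266 and baseline 1.0 gives 258, close to the stated 230, 262 and 260 but not equal. The article states no such follow-up.

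**Step 4: power at 239 per arm.** Power = Φ(0.2847/√{[2.0614/t + 2d]/239} − 1.960).

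- d = 0.46, t = 1: 0.2847/0.1117 = 2.549, power 72%.
- d = 2.17, t = 1: 0.2847/0.1638 = 1.739, power 41%.
- Shape reading at other follow-up times: 33% at half a year, 48% at two years, 56% with unlimited follow-up.
- Shape reading over k = 0.34 to 0.60 at one year: 35% to 47%, with 769 down to 522 per arm needed for 80%.

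A simulation of 1,500 trials with a maximum-likelihood negative binomial Wald test gave 70% for the dispersion reading and 41% for the shape reading.

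**The case against.** The strongest reply is that this is one wrong word in a parenthesis. The sizes show that the calculation treated k as a dispersion. If the cited reanalysis also reports a dispersion, the label cost no power. The label also enters no analysis: the Data analysis section checks model fit against a simulated residual envelope and does not compare the fitted k with 0.46. Recruitment has finished at 522, so the size cannot change.

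Most of this stands. A reader might infer that the trial has only 41% power, but the article does not support that. The 41% applies only if the source's 0.46 is a shape, and it assumes one year of follow-up. Nor is the whole distance from 80% to 41% due to the label: at one year the dispersion reading already falls to 72%, because 239 does not reproduce. If the formula is rescaled so that the dispersion reading gives exactly 80% at 239, the shape reading gives about 48%.

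A reader might also infer that relabelling puts the section right. It does not, since it restores the direction of the sizes but not their level.

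The reply does not remove the contradiction. Nothing else in the article says which convention the source uses, and the shape reading cannot produce the stated sizes at any follow-up time.

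**Conclusion.** The point holds as an internal contradiction: the definition of k and the 230, 239, 262 sequence cannot both be right. That conclusion is algebraic and rests on no assumption about follow-up, sidedness or test. The label is the likelier error, but only the cited reanalysis can confirm it.

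The effect on power depends on which branch is true, and the figures rest on the assumptions listed in the working. At 239 per arm and one year it is about 72% if 0.46 is a dispersion and about 41% if it is a shape. The second figure moves with the assumed follow-up time and with k, and should be quoted only with those conditions. The correction is worth making because k is the sole variability input and the section cannot be re-derived as it stands.

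**What to change.** Check how the cited reanalysis parameterises k. Then, in the Sample size section, state the parameterisation explicitly together with the variance formula, sidedness and follow-up time per person, and restate the power to match.

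- **If 0.46 is a dispersion:** replace the shape wording with a dispersion parameter, variance mu + k·mu², reciprocal of the gamma shape. Also either show the settings that give 239 or restate the power; at one year, two-sided, it is about 72% at 239 per arm.
- **If 0.46 is a shape:** correct the sensitivity figures, say that the low end of 0.34 to 0.60 is the worst case, and restate the power at 239 per arm: about 41% at one year (33% at half a year, 48% at two years; 35% to 47% over the interval at one year). These figures are for 239 per arm. The 522 enrolled, about 261 per arm, would give about 44% at one year before dropout.

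The cost is a source check and a few corrected sentences. No extra patients are needed. The only downside is a possibly less favourable stated power.
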